### 2.2. Participants and Sample Size

Individuals from the general population (age range: 18–60 years) exhibiting unhealthy lifestyles and behaviors (i.e., heavy smoking, heavy drinking, and dysfunctional eating behaviors) and are at risk for nicotine dependence, alcohol abuse, or eating disorders will be recruited via social media by filling an online battery of self-report psychometric questionnaires (administered via the Qualtrics online platform).

The inclusion criteria will include the following: (a) being between 18 and 60 years of age; (b) having no prior diagnosis according to the DSM-5-TR [33] diagnostic criteria; (c) displaying one of the unhealthy lifestyles and behaviors mentioned above according to the relative screening questionnaires (see Screening measures below).

The exclusion criteria will include the following: (a) lack of capacity to consent for research; (b) current or former diagnosis of psychiatric disorders according to the DSM-5-TR diagnostic criteria; (c) using medical devices (e.g., pacemaker and hearing aids) or having a medical condition (e.g., vertigo and vision impairments) that may interfere with VR technologies; (d) having concurrent physical health conditions that might better explain the presence of these unhealthy behaviors.

Participants will be enrolled until reaching a number of around 64 individuals for each of these three separate samples: (1) individuals who engage in heavy smoking, (2) individuals who engage in heavy drinking, and (3) individuals who report dysfunctional eating behaviors. The sample size was calculated using G*Power [34] and considering our main statistical analyses (repeated measure ANOVAs with a medium effect size of 0.25, power of 0.80, two groups, and four time measurements), with an addition of an estimated 30% drop-out rate.

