
### 2.6. Data Analyses

Data analyses will be performed using SPSS Statistic vrs.28. Data analyses will be performed separately for the three samples that are included in the study (i.e., individuals who engage in heavy smoking, heavy drinking, and dysfunctional eating behaviors).

Descriptive statistics will be run to analyze socio-demographics (age, marital status, educational level, and occupational status), clinical characteristics (BMI, former DSM-5-TR diagnosis, clinical conditions, and/or the use of medical devices interfering with VR), and mean FTND, AUDIT, SCOFF, and EDE-Q scores in the relative groups. The mean DERS-16, AAQ-II, MPFI-EA, and DASS-21-stress scale scores will also be calculated for all samples separately.

To test pre-intervention differences between the experimental and control groups (waiting-list condition) in each sample, Chi-squares will be performed on categorical variables, whereas ANOVAs will be performed on continuous variables.

To test the effects of the VR-based intervention, changes over time in the relevant unhealthy behavior (FTND, AUDIT, or SCOFF and EDE-Q scores), in transdiagnostic factors (DERS-16, AAQ-II, and MPFI-EA scores), and in stress levels (DASS-21-stress scale scores) will be assessed in the experimental group of the samples using a priori contrast analysis. In particular, we plan to compare each assessment time (T0, T1, T2, and T3) against each other. The percentage of drop-out cases will be calculated.

To test the efficacy of the VR-based intervention compared to the control (waiting-list) condition, changes between the experimental and control (waiting-list) groups of the samples in the relevant unhealthy behavior (FTND, AUDIT, and EDE-Q scores), in transdiagnostic factors (DERS-16, AAQ-II, and MPFI-EA scores), and in stress levels (DASS-21-stress scale scores) will be tested by performing repeated measure ANOVAs using time (T0, T1, T2, and T3) as a within-subject factor and group assignment (experimental/VR vs. control) as a between-subject factor. To control for Type 1 error in within-group mean contrasts, the Bonferroni correction will be applied.

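### Bonferroni over the six pairwise visit contrasts is valid, but a step-down rule gives the same family-wise guarantee with somewhat more power for the within-arm contrasts (cheap improvement, not an error)

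*Protocol article*

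**What the plan says.** Section 2.6 of the protocol article sets out two separate lines of analysis, each run separately in the three behaviour samples.

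- **Within the VR arm.** Changes over time "will be assessed in the experimental group of the samples using a priori contrast analysis", and "we plan to compare each assessment time (T0, T1, T2, and T3) against each other".
- **Between arms.** A second line begins "To test the efficacy of the VR-based intervention compared to the control (waiting-list) condition" and uses repeated-measures ANOVAs with time and group, followed by MANOVAs and MANCOVAs.

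The multiplicity rule is one sentence: "To control for Type 1 error in within-group mean contrasts, the Bonferroni correction will be applied". It gives no alpha level, no divisor and no definition of the family.

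Section 2.2 bases the sample size of around 64 per behaviour sample on the repeated-measures ANOVA, "with a medium effect size of 0.25, power of 0.80, two groups, and four time measurements" and "with an addition of an estimated 30% drop-out rate". The visit contrasts play no part in that calculation.

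**The concern.** Plain Bonferroni holds each of the six contrasts to the same threshold, whatever the other five show. The six hypotheses are logically linked: if any one pair of the four visit means truly differs, at most three of the six equalities can still be true. After a correct first rejection, a divisor of 6 is therefore twice what 5% family-wise control requires.

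What is at stake is power for secondary but useful questions. Section 2.3 says the follow-ups are there to see whether changes last, and within the VR arm that is read from contrasts such as T0–T3 and T1–T3. With few participants per arm, a true change or a true loss of benefit at follow-up is missed somewhat more often than the error guarantee requires.

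**Working it through.** **Inputs from the article.** Four assessments, all compared with each other; Bonferroni for within-group contrasts; about 64 per sample; 30% drop-out.

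**Assumptions.** Two-sided 5% level; the family is the six contrasts of one outcome; 1:1 allocation; normal scores with equal variances. The article gives no effect size or between-visit correlation for these contrasts, so those below are also assumed.

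**Number per arm.** 64/2 = 32 randomised. With 30% loss, 64 × 0.70 / 2 = 22.4, about 22.

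**Implied threshold.** Pairs = 4 × 3 / 2 = 6, and 0.05/6 = 0.0083. Check: 6 × 0.00833 = 0.05, so Bonferroni controls the family-wise error. The article prints no threshold to reproduce.

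**Step-down divisors.** Among four means the possible numbers of true equalities are 6 (all equal), 3 (three equal, one apart), 2 (two equal pairs), 1 and 0. Order the p-values from smallest to largest:

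| Step | Bonferroni | Holm | Shaffer |
|---|---|---|---|
| 1 | 0.05/6 = 0.0083 | 0.05/6 = 0.0083 | 0.05/6 = 0.0083 |
| 2 | 0.0083 | 0.05/5 = 0.0100 | 0.05/3 = 0.0167 |
| 3 | 0.0083 | 0.05/4 = 0.0125 | 0.05/3 = 0.0167 |
| 4 | 0.0083 | 0.05/3 = 0.0167 | 0.05/3 = 0.0167 |
| 5 | 0.0083 | 0.05/2 = 0.0250 | 0.05/2 = 0.0250 |
| 6 | 0.0083 | 0.0500 | 0.0500 |

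No step-down threshold is below Bonferroni's, so every Bonferroni rejection is kept.

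**Power per true contrast** (%; paired t-tests, 20,000 simulated trials per setting). Pattern = change from T0 in SD at T1, T2, T3; r = correlation between visits. A dash means not tabulated.

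| Pattern | n | r | Contrast | Bonferroni | Holm | Shaffer | Shaffer gain |
|---|---|---|---|---|---|---|---|
| 0.3 sustained | 22 | 0.5 | from T0 | 9 | – | 11 | 2 |
| 0.3 sustained | 32 | 0.5 | from T0 | 15 | – | 18 | 3 |
| 0.5 sustained | 22 | 0.5 | from T0 | 31.7 | 34.0 | 37.6 | 5.9 |
| 0.5 sustained | 32 | 0.5 | from T0 | 51.5 | 54.6 | 58.7 | 7.2 |
| 0.6 sustained | 22 | 0.5 | from T0 | 48 | 51 | 55 | 7 |
| 0.8 sustained | 22 | 0.5 | from T0 | 78.6 | 81.9 | 85.1 | 6.5 |
| 0.8 sustained | 32 | 0.5 | from T0 | 94.8 | 96.1 | 97.1 | 2.3 |
| 0.5, 0.4, 0.3 | 32 | 0.5 | T0–T3 | 14.9 | 17.2 | 20.6 | 5.7 |
| 0.8, 0.6, 0.4 | 22 | 0.5 | T1–T3 | 18 | 22 | 26 | 8 |
| 0.8, 0.6, 0.4 | 32 | 0.7 | T0–T3 | 55 | 66 | 67 | 12 |

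For a sustained 0.2 SD change at n = 32 the Shaffer gain is about 1 point.

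**At least one true change detected** (Bonferroni / Holm / Shaffer). 0.5 SD sustained: 56.5 / 56.5 / 56.7% at n = 22 and 77.4 / 77.5 / 77.5% at n = 32. This is practically unchanged, because step 1 is the same under all three rules.

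**Family-wise error.** All means equal: 0.044 under each rule. Three means equal and T0 apart, same order of rules: 0.026 / 0.033 / 0.043 (0.5 SD, n = 22) and 0.024 / 0.044 / 0.046 (0.8 SD, n = 32). All are below 0.05. In these settings Bonferroni uses about half of the permitted error, and that unused half is the source of the power gain.

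**The case against.** The strongest reply is that nothing here is wrong. Bonferroni is valid, prespecified and conservative, and it does what the sentence says it is for. No other passage contradicts it, and the same refinement could be suggested for almost any plan that uses it. All of that stands.

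Four further points also stand.

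- The 0.05/6 threshold is inferred. A condensed article may leave alpha and the family to a fuller document.
- The contrasts are uncontrolled changes within the VR arm. More rejections there add nothing to the evidence that VR beats the waiting list.
- Step-down rules have a cost. Bonferroni comes with simple simultaneous confidence intervals that agree with its tests. Unadjusted 95% intervals shown beside step-down decisions can exclude zero where the test does not reject. The ordering must also be done outside the default SPSS output, for each outcome in each of three samples.
- The largest gain comes from one contrast in one assumed pattern. The n of 22 assumes complete cases, whereas the article states an intention-to-treat approach.

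A reader might infer that the plan loses error control, that the efficacy comparison is underpowered because of this correction, or that the change is free. The documents support none of these: the correction is valid, it is worded for within-group contrasts only, and the sample size rests on the ANOVA.

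What the reply does not remove is that, for test decisions, the planned rule is never better and often worse than an alternative with the same 5% guarantee that uses p-values from contrasts already planned.

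**Conclusion.** The point holds as a low-priority improvement, not as an error. For six pairwise visit contrasts per outcome, Bonferroni is dominated in test decisions by Holm, and Holm by Shaffer's rule for four means.

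With Shaffer the gain per true contrast is about 1 to 3 points for small effects and mostly 4 to 8 for moderate sustained effects (about 3 with Holm). It is less where power is already near 100%, and reaches about 12 points in one fading-effect setting. The chance of detecting any change at all stays the same.

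These sizes depend on the assumed effects, correlations, 1:1 allocation and two-sided 5% level. That the step-down rules reject at least as much under the same guarantee does not depend on the effects or correlations. The VR versus waiting-list analyses and the figure of around 64 per sample do not change.

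**What to change.** In section 2.6, replace the Bonferroni correction for the within-group contrasts with one of the following, and state the alpha level and that the family is the six visit contrasts of one outcome:

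- **Shaffer's step-down for four means:** order the six unadjusted p-values and test them against 0.05 divided by 6, 3, 3, 3, 2 and 1, stopping at the first non-significant one. All six contrasts must concern the same four means, so draw them from the same analysis set.
- **Holm:** the same procedure with divisors 6, 5, 4, 3, 2 and 1. It gains a little less but does not rely on the logical links between the contrasts.

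The wording should be fixed before outcome data are analysed by arm. It costs one sentence, plus a short ordering step on p-values that SPSS already produces. If intervals are reported, say whether they are unadjusted, because they will not match the step-down decisions exactly. If matching simultaneous intervals matter more to the team than the extra power, keeping Bonferroni is defensible, and stating the alpha and the divisor would then be enough.

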Moreover, to also take into consideration the possible multivariate nature of the involved variables and the association between dysfunctional behaviors, transdiagnostic factors, and stress, we will perform repeated measures MANOVAs using time (T0, T1, T2, and T3) as a within-subject factor, group assignment (experimental/VR vs. control) as a between-subject factor, and questionnaire scores (one between FTND, AUDIT, or EDE-Q scores depending on the sample, as well as DERS-16, AAQ-II, and MPFI-EA for transdiagnostic factors and DASS-21 for stress) as five dependent variables.

MANCOVAs will also be performed to compare the mean levels of relevant unhealthy behavior (FTND, AUDIT, or SCOFF and EDE-Q scores), transdiagnostic factors (DERS-16, AAQ-II, and MPFI-EA scores), and stress levels (DASS-21-stress scale scores) of the experimental and control (waiting-list) groups of the samples at each assessment time (T1, T2, and T3), adjusting for any differences at T0 and age. In particular, three MANCOVAs will be run (one for T1 scores, one for T2 scores, and one for T3 scores) for each sample relative to the dysfunctional behaviors using group (VR or waiting-list) as an independent variable, questionnaire scores (one between FTND, AUDIT, or EDE-Q scores depending on the sample, the questionnaires DERS-16, AAQ-II, and MPFI-EA for transdiagnostic factors and the DASS-21 for stress) as five dependent variables, and scores at T0 and age as covariates.

All analyses will be performed following an Intention-To-Treat (ITT) approach in order to preserve the randomized design and provide a more conservative estimate of treatment effects.

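### Intention-to-treat is promised for all analyses, but the main efficacy tests need complete data at all four visits and no missing-data method is stated to reconcile the two

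*Protocol article*

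**What the plan says.** All statements are in the protocol article.

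- **Analysis population** (2.6 Data Analyses): "All analyses will be performed following an Intention-To-Treat (ITT) approach in order to preserve the randomized design". The same sentence adds that this gives a more conservative estimate of the treatment effect.
- **Between-arm efficacy test** (2.6): "repeated measure ANOVAs using time (T0, T1, T2, and T3) as a within-subject factor", with arm as the between-subject factor.
- **Multivariate test** (2.6): "repeated measures MANOVAs using time (T0, T1, T2, and T3) as a within-subject factor", on five dependent variables (the relevant behaviour score, DERS-16, AAQ-II, MPFI-EA and DASS-21).
- **Per-visit test** (2.6): "three MANCOVAs will be run (one for T1 scores, one for T2 scores, and one for T3 scores", for each sample, adjusted for T0 scores and age.
- **Software** (2.6): "Data analyses will be performed using SPSS Statistic vrs.28".
- **Drop-out in the analysis section** (2.6): "The percentage of drop-out cases will be calculated". Nothing else is said there about missing data.
- **Drop-out in the sample size** (2.2 Participants and Sample Size): about 64 per sample in three samples, "with an addition of an estimated 30% drop-out rate".

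**The concern.** Classical repeated-measures ANOVA and MANOVA, as fitted by the SPSS general linear model, remove any participant who lacks one of the repeated scores. A participant who finishes treatment, answers at T1 and misses only the 6-month questionnaire is lost from both tests. The article fixes the model, visits, factors, software and population, and that combination does not deliver the population it names. The issue is therefore a conflict between stated choices, not a detail left to another document.

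At stake is the randomised comparison in all three samples and on every outcome. Adding participants to cover drop-out restores power but does not bring the drop-outs back into the comparison. The two arms carry different burdens: six weekly laboratory sessions with homework in one, telephone check-ups in the other (section 2.4). Reasons for leaving could therefore differ by arm. The result would carry an intention-to-treat label and a claim of conservatism that the method does not guarantee.

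**Working it through.** **1. The plan's own sample size.** Inputs from 2.2: effect size f = 0.25, power 0.80, two groups, m = 4 measurements, 30% drop-out. Not stated, so assumed: alpha 0.05, sphericity, and the correlation rho between repeated measures. For the group-by-time interaction, lambda = f² × N × m / (1 − rho), with (m − 1) and (N − 2)(m − 1) degrees of freedom.

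- rho = 0: N = 45 gives power 0.80, and 45 / 0.70 = 64.3, in line with about 64.
- rho = 0.5: N = 24, and 24 / 0.70 gives 35.

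So 64 can be reached, but only with an unstated low correlation. With 45 analysed, interaction power is 0.80 (rho = 0) or 0.984 (rho = 0.5). Power has been allowed for; the question is who is compared.

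**2. Numbers entering the complete-data tests.**

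- Per sample: 64 × 0.70 = 44.8, about 45, or about 22 per arm if allocation is 1:1 (ratio not stated).
- Left out: 64 × 0.30 = 19.2, about 19 per sample.
- Overall: 192 × 0.70 = 134.4, about 134.
- Scores needed from each person for the MANOVA: 5 outcomes × 4 visits = 20.

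This assumes that everyone counted as a drop-out misses at least one questionnaire. Scattered missed visits by others would lower the figures. Drop-outs who still answer online would raise them.

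**3. Who enters which analysis (no imputation).**

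| Analysis | Included |
|---|---|
| ANOVA over T0–T3 | those with that outcome at all four visits |
| MANOVA over T0–T3 | those with all 20 scores |
| MANCOVA at T1, T2 or T3 | those with all scores at that visit, T0 scores and age |

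A person seen at T1 and lost later is in the T1 MANCOVA but in neither the ANOVA nor the MANOVA. No row covers all randomised participants.

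**4. Possible bias.** The documents give no drop-out mechanism, so these are illustrations: 32 per arm, no true effect, drop-out of about 25–30%, rho 0.5 to 0.6, control drop-out random. The quantity is the completers' arm difference in change from T0, which is what the group-by-time test uses.

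| Drop-out in the VR arm | Bias in change from T0 |
|---|---|
| Random | about 0 |
| Driven by last observed score | up to about 0.07 SD at T1 and T2, near zero at T3 |
| Driven by worsening since T0 | 0.22–0.30 SD at T1; about 0.12–0.20 SD at T3 |

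Two checks, assuming a constant correlation:

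- *Worsening.* Cov(Y3 − Y0, Y1 − Y0) = 1 − rho and Var(Y1 − Y0) = 2(1 − rho). If drop-out follows T1 change, the T3 bias is half the T1 bias. A T3 bias of 0.13 SD implies 0.26 SD at T1, inside the range shown.
- *Last score.* If all drop-out follows the T1 score and shifts the completers' T1 mean by d, their T0 mean shifts by rho × d, leaving (1 − rho) × d in the change. With d = 0.25 and rho = 0.6 this is 0.10 SD. So 0.07 describes the runs made and is not a ceiling.

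For scale, with 22.4 per arm the standard error of the difference in change is √[2(1 − rho)] × √(2 / 22.4), which is 0.30 SD at rho = 0.5 and 0.27 SD at rho = 0.6. The largest biases are about one standard error.

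**5. The T0-adjusted comparison at T1.** With drop-out driven by the last score, a single-outcome T1 analysis adjusted for T0 showed bias below 0.01 SD. At T2 and T3 about 0.02–0.08 SD remained.

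**The case against.** **Complete-case analysis is inferred.** The article names neither listwise deletion nor an SPSS procedure. Imputing before the ANOVA would satisfy the intention-to-treat sentence, and a fuller document might say so. This stands as a caveat. It does not remove the conflict, because this text states the methods and the population together and gives no step that joins them.

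**The Abstract speaks of a mixed-model repeated-measures analysis of variance.** Sections 2.2 and 2.6 show that this means one within-subject and one between-subject factor, not a likelihood-based mixed model.

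A reader might also infer four stronger points that the documents do not support:

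- *That T1 data from later drop-outs are thrown away.* The T1 MANCOVA uses them.
- *That completers would show a false VR advantage of about 0.25 SD.* In the last-score scenario that figure is a raw difference in levels at T1, and it comes with an imbalance of 0.19 SD at T0. The planned test concerns change: 0.25 − 0.19 = 0.06 SD at T1 and 0.18 − 0.19, about zero, at T3.
- *That the bias favours VR.* That direction is built into the assumed mechanism. The documents give no reason why people would leave.
- *That adding 30% for drop-out shows that a completers' analysis is intended.* Trials analysed by mixed models also inflate for drop-out.

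Nor can a smaller standard error at T1 (0.24 against 0.29 SD) be credited to retained data alone: adjusting completers for T0 gave the same reduction.

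**Conclusion.** The conflict holds. As written, the ANOVA and MANOVA that carry the efficacy claim would rest on about 45 of 64 participants per sample (about 134 of 192), while the plan says that every analysis is intention-to-treat. This assumes that missing values are not imputed and that the 30% all miss at least one questionnaire. The per-visit MANCOVAs soften the loss, above all at T1, but use changing subsets.

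The bias is uncertain in size and direction: from about zero (random drop-out), through less than 0.1 SD in the last-score runs, to roughly 0.1–0.3 SD (worsening in one arm). All of these rest on assumed mechanisms. They are enough to say that a more conservative estimate is not assured, and not enough to say that VR would be favoured. Power is not the problem.

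**What to change.** 1. Make the efficacy analysis a likelihood-based mixed model for repeated measures (SPSS MIXED) with arm by visit and an unstructured covariance, separately in each sample. Include all randomised participants, for example by treating T0 as a response with a common mean in the two arms. A model limited to participants with a post-baseline value would again drop those lost before T1. Alternatively, use multiple imputation for participants with no post-baseline value.
2. Report the arm difference at T1, T2 and T3 from that model.
3. Add a sensitivity analysis for data missing not at random.
4. Keep the complete-case ANOVA and MANOVA as sensitivity analyses only, labelled as such, and state which participants each MANCOVA includes.
5. Delete the claim that the approach is more conservative.

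**Cost:** a different SPSS procedure, a paragraph of text and slightly more analysis work. No additional participants or assessments are needed. The main analysis would assume data missing at random, which cannot be verified; item 3 addresses that.

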## 3. Discussion and Clinical Implications

Unhealthy lifestyles and behaviors such as heavy drinking, smoking, and engaging in dysfunctional eating behaviors (e.g., bingeing and excessive dieting) are highly associated with health-related issues and risks [57,58,59]. Because of this, and also due to the observed increase in these unhealthy lifestyles and behaviors following the COVID-19 pandemic [60,61,62], improving the accessibility and reach of current psychological interventions to reduce smoking, alcohol use, and dysfunctional eating behaviors is of particular clinical relevance.

According to the literature, VR is a promising instrument to reduce these behaviors in several studies [5,6,25,26,27,28,29,30]. However, the disorder-specific approach that has been used for the development of VR software and interventions (with the exception of those developed to improve emotion regulation strategies [8]) has resulted in high implementation costs for their use in clinical psychology and has limited their application [63].

Applying a transdiagnostic approach to the development of VR software could help to overcome this issue. In fact, due to its ability to overcome some of the flaws concerning disorder-specific treatments (such as higher costs in terms of time and training and the need for multiple protocols aimed at tackling specific psychiatric diagnoses), the transdiagnostic approach has already gained support in the field of clinical psychology [64,65]. Since the H.O.M.E. software and the related VR-based intervention were created to be able to tackle several unhealthy lifestyles and behaviors (e.g., heavy drinking, smoking, and engaging in dysfunctional eating behaviors) together with several transdiagnostic factors linked to their maintenance (i.e., psychological flexibility, emotion regulation, and experiential avoidance), these instruments could be useful tools for clinicians to help more individuals to improve their health and well-being. Moreover, given the similarities between VR and technologies used in everyday life (e.g., smartphones and videogames), the tested VR-based intervention may help engage individuals who are reluctant towards traditional psychological prevention strategies, especially young people. In conclusion, if the expected beneficial effect of the H.O.M.E. protocol is confirmed after this research protocol, a new instrument to address psychological distress, unhealthy behaviors, and transdiagnostic psychological risk factors will be available, which could provide major advancements in the promotion of well-being in adults and young individuals [66,67].

